**List of abbreviations and relevant definitions**

|                           |                                                                                                                                                                                                                                                                                                                                           |
|---------------------------|-------------------------------------------------------------------------------------------------------------------------------------------------------------------------------------------------------------------------------------------------------------------------------------------------------------------------------------------|
| AE                 | Adverse Event                                                                                                                                                                                                                                                                                                                             |
| ALA-patch          | Cutaneous patch with 5-aminolevulinic acid                                                                                                                                                                                                                                                                                                |
| APACHE             | Acute Physiology and Chronic Health Evaluation                                                                                                                                                                                                                                                                                            |
| BP                 | Blood pressure                                                                                                                                                                                                                                                                                                                            |
| CE                 | Conformité Européene, declaration that the medical product complies with the essential requirements of the European Directive                                                                                                                                                                                                             |
| COMET              | Cellular Oxygen METabolism                                                                                                                                                                                                                                                                                                                |
| DSMB               | Data Safety Monitoring Board                                                                                                                                                                                                                                                                                                              |
| EPD                | Electronic patient dossier                                                                                                                                                                                                                                                                                                                |
| ICH-GCP            | International Conference on Harmonisation of Technical Requirements for Registration of Pharmaceuticals for Human Use - Good Clinical Practice guideline                                                                                                                                                                                  |
| HF                 | Heart frequency                                                                                                                                                                                                                                                                                                                           |
| ICU                | Intensive Care Unit                                                                                                                                                                                                                                                                                                                       |
| MC                 | Medium Care                                                                                                                                                                                                                                                                                                                               |
| METC               | Medical research ethics committee (MREC); in Dutch: medisch ethische toetsing commissie (METC)                                                                                                                                                                                                                                            |
| MitoPO2 | Mitochondrial oxygen tension                                                                                                                                                                                                                                                                                                              |
| NFU                | Nederlandse Federatie Universitair Medisch Centra                                                                                                                                                                                                                                                                                         |
| P(a)O2  | Arterial oxygen tension                                                                                                                                                                                                                                                                                                                   |
| PpIX               | Protoporphyrine IX                                                                                                                                                                                                                                                                                                                        |
| (S)AE              | (Serious) Adverse Event                                                                                                                                                                                                                                                                                                                   |
| SaO2    | Arterial saturation                                                                                                                                                                                                                                                                                                                       |
| SpO2    | Peripheral measured oxygen saturation                                                                                                                                                                                                                                                                                                     |
| Sponsor            | The sponsor is the party that commissions the organization or performance of the research, for example a pharmaceutical company, academic hospital, scientific organization or investigator. A party that provides funding for a study but does not commission it is not regarded as the sponsor, but referred to as a subsidizing party. |
| TSLT               | Triplet State Lifetime Technique (protoporphyrin IX-triplet state lifetime technique)                                                                                                                                                                                                                                                     |
| WMO                | Medical Research Involving Human Subjects Act (in Dutch: Wet Medisch-wetenschappelijk Onderzoek met Mensen)                                                                                                                                                                                                                               |

## Summary

**Rationale:** Recent studies have shown the potential of a protoporphyrin IX-triple state lifetime technique to measure mitochondrial oxygen tension (mitoPO2) in vivo, which possibly is an early indicator of oxygen disbalance in the cell. With the advent of the COMET measurement system, steps have been made to determine the feasibility of this measurement method. The INOX ICU-2 study (parent study) aims to tailor transfusion therapies to individual intensive care unit (ICU) patients based on mitochondrial oxygen tension. In the pilot study of the INOX ICU-2 study, in which the COMET measurement system was used on critically ill patients receiving red blood cell transfusion, an increase in the between- and within-subject variability was observed over time. This deviation was not explored during the development of the COMET measurement system. Therefore, we aim to determine the between- and within-subject variability of this measurement in healthy subjects and in hemodynamically stable subjects at the intensive care unit.

**Main objectives:** To describe the between- and within-subject variability of mitoPO2 measurements during a 24 hour period after 5- aminolevulinic acid (ALA)-induction among healthy volunteers and among neurosurgical patients admitted postoperatively to the ICU or MC. Healthy subjects allow for the exploration of the effect of time-since-application of ALA-patch and neurosurgical patients allow for the exploration of a possible effect of ICU-admittance.

**Study design:** Prospective cohort study.

**Study population:** Healthy volunteers and neurosurgical patients admitted at the ICU or Medium Care(MC) of LUMC after surgery.

### Main study endpoints:

Primary endpoint:

- Between- and within-subject variability (assessed by standard deviation) of mitoPO2 measurements over a period of 24 hours after ALA-induction.
  - o Initially in healthy volunteers
  - o Followed by neurosurgical patients admitted postoperatively to the ICU or MC.

Secondary endpoints:

- Description of the differences in the between- and within-subject variability between 3 hour offset ALA-patches.
- Description of between- and within-subject variability in healthy volunteers and neurosurgical patients in relation to the between- and within-subject variability of the INOX ICU-2 pilot study (P16.303)
- Report on adverse and serious adverse events of the mitoPO2 measurements.

**Study procedure:** MitoPO2 measurements will be taken in healthy volunteers using two ALA-patches offset to each other by 3 hours, this has been done to observe possible differences in measurements at different time-points after ALA-induction while maintaining other variables stable. Following the healthy volunteers, neurosurgical patients will be included. Patients will undergo neurosurgery as planned and common practice is that no major interventions are needed in the postoperative phase on the ICU/MC. At multiple predefined moments after surgery, mitoPO2 measurements will take place, again using two ALA-patches with a 3 hour offset.

**Nature and extent of the burden and risks associated with participation, benefit and group relatedness:** The risks are small in this study with no serious adverse events (SAE) known. The burden for participants is small since it involves a non-invasive measurement. We will perform this study first in health volunteers. Following the healthy volunteers, neurosurgical patients will be included. Patients will undergo neurosurgery as planned and common practice is that no major interventions are needed in the postoperative phase on the ICU. Normal clinical practice will continue and will not be altered. These patients will allow for the exploration of a possible effect of ICU admittance.

## 1. Introduction and rationale

Adequate tissue oxygenation is one of the cornerstones of therapy in critical care medicine, which is guided by intensive monitoring. Monitors are used to assess global oxygen delivery and thus the macrocirculation. However, tissue oxygenation is multifactorial and depends not only on the macrocirculation but also on the microcirculation and local cellular oxygen consumption. In critically ill intensive care unit (ICU) or medium care (MC) patients disturbances in the microcirculation may lead to cellular hypoxia. While it is currently possible to monitor cellular oxygenation, these techniques are still in their infancy.

Mik et al. have recently introduced the protoporphyrin IX (PpIX)-triplet state lifetime technique as the first method to measure mitochondrial oxygen tension (mitoPO2) in living cells and tissues. Experimental results have shown mitoPO2's robustness and clinical potential as a parameter for cellular function. Animal research has shown that mitoPO2 is a capable predictor of lactate increase. With the advent of the COMET measurement system, bedside monitoring of mitoPO2 might allow for therapies to be tailored to individual patients.

During the pilot study of the ongoing INOX ICU-2 study an increase in the variation of mitoPO2 results within one subject at each time point (within-subject variability) was observed the longer the 5-aminoulinic acid (ALA)-patch was in place (see appendix 1, table 1). The mean within-subject variability was 3.0 mmHg at baseline (before red blood cell (RBC) transfusion), 3.5 mmHg 2 hours after RBC transfusion and eventually increased to 7.3 mmHg 3 hours after RBC transfusion. Twenty-four hours after RBC transfusion an even higher within-subject variability of 8.7 mmHg was seen. Similarly, the variation over the group at each time point of mitoPO2 measurements (between-subject variability) seemed stable initially, but increased after 2 hours. The mean between-subject variability was 13 mmHg at baseline, 15.7 mmHg in the first hour after transfusion and gradually increased to 28.2 mmHg after 3 hours, up to 42.5 mmHg after 24 hours (see appendix 1, table 1 and figure 1).

After this result, we hypothesized why the within-subject variability increased over time. The increased within-subject variability might have been the consequence of a decreased measurement sensitivity, since animal studies have shown normalization of PpIX levels after 24 hours of ALA induction, thereby limiting the PpIX phosphorene detectability. However, this was probably not the case, as the median signal quality after 24 hours was still above the required 30% (median 46, IQR 34-64.5%). The increased between-subject variability might have been the consequence of different changes in the oxygen supply to the cells in the different patients over time as well. It is known that the intracellular oxygen content is dependent on multiple factors. This oxygen supply can change dramatically in 24 hours due to the underlying disease and multiple other interventions besides the red blood cell transfusion.

To determine the reason of the increased within-subject variability, it would be ideal to repeat the measurements in healthy volunteers and in a cohort of patients admitted to the ICU that are expected to receive minimal interventions. In the Leiden University Medical Center, neurosurgical patients are admitted to the ICU or MC postoperatively. This cohort of patients consists of the most hemodynamically stable patients and receives the least amount of interventions compared to other cohorts of patients in the ICU or MC. Therefore, the cohort of neurosurgical patients would be ideal to investigate the course of the between- and within-subject variability of mitoPO2 during a period of 24 hours. Measurements will initially be carried out in a cohort of healthy volunteers to evaluate the effect of time-since-application and continued in the neurosurgical patients to factor in the effect of ICU admittance, including the standard interventions patients admitted to the ICU receive. In the pilot a large increase in the between- and within-subject variability was observed after 3 hours. To account for influence of the ALA-patch on the measurement variability, 2 ALA-patches will be used offset relative to each other by 3 hours. This offset of 3 hours was chosen since an increase in between- and within-subject variability was observed after 3 hours in the INOX ICU-2 pilot study.

## 2. Objectives

### 2.1 General

The aim of this project is to describe the between- and within-subject variability, as assessed by the standard deviation, of mitoPO2 measurements during a period of 24 hours after ALA-induction with the COMET measurement system (see section 7.2), initially in healthy volunteers, followed by postoperative neurosurgical patients admitted to the ICU or MC. Healthy subjects allow for the exploration of the effect of time-since-application of ALA-patch and neurosurgical patients allow for the exploration of a possible effect of ICU-admittance, including the effect of interventions patients admitted to the ICU receive. Furthermore, we will compare this to the already observed change over 24 hours of mitoPO2 in patients who received red blood cell transfusion in the ICU.

### 2.2 Endpoint

In this descriptive study we aim to investigate mitoPO2's variability over the 24 hour period after ALA-induction

Specific objectives:

1. To describe the between- and within-subject variability (assessed by standard deviation) of mitoPO2 measurements over a period of 24 hours after ALA-induction.
  - a. Initially in healthy volunteers
  - b. Followed by neurosurgical patients admitted postoperatively to the ICU or MC.
2. To describe the between- and within-subject variability between 3 hour offset ALA-patches.
3. Description of between- and within-subject variability in healthy volunteers and neurosurgical patients in relation to the between- and within-subject variability of the INOX ICU-2 pilot study (P16.303).
4. Report on adverse and serious adverse events of the mitoPO2 measurements.

### 3. Design and population

#### 3.1 Study design

We will prospectively study the between- and within-subject variability of mitoPO2 measurements in the Leiden University Medical Center (LUMC). Initially, measurements will be taken among 17 healthy volunteers at predefined moments over a 24 hour period, to observe the between- and within-subject variability. Subsequently, clinical measurements will commence to factor in the critical care setting. Measurements will be taken among 17 patients, admitted to the ICU or MC after neurosurgery, at predefined moments during the first 24 hours after admittance. No specific interventions besides standard care will be performed. During the study, nurses and clinicians will be blinded for the results of the mitoPO2, since the investigators execute the mitoPO2 measurements and will not reveal the results.

**Figure 1:** Gross overview of the study design on healthy volunteers

[figure not shown]

**Figure 2:** Gross overview of the clinical study design in neurosurgical patients[figure not shown]

## 4. Study population

### 4.1 Population (base)

The study population will consist, initially, of healthy volunteers. This group was chosen to perform measurements on, to eliminate the effect of critical illness and interventions on the ICU and to better explore the effect of time-since-application of the ALA-patches. Neurosurgical ICU/MC patients will subsequently be included to further explore the effect of critical illness (ICU admission). Since this cohort of patients receives minimal interventions, they are ideal to limit potential affecters on the between- and therefore also the within-subject variability.

This study population will consist of patients undergoing elective neurosurgery with planned postoperative recovery of at least 24 hours in the ICU or MC. The LUMC is a neurosurgical center in which a wide variety of surgeries including tumor resection in the posterior cranial fossa (including vestibular schwannoma) are performed. These patients need to be monitored postoperatively due to the risk of bleeding, infections and the need for mechanical ventilation. Clinical experience has shown that this cohort of patients are in general, hemodynamically the most stable patients and receive the least amount of interventions compared to other cohorts of patients in the ICU or MC. Furthermore, it is important to evaluate the COMET measurement system's performance in the clinical setting. For these reasons, the cohort of elective neurosurgical patients would be ideal to investigate the reason of the increased between- and within-subject variability of mitoPO2 in the ICU and MC setting.

### 4.2 Inclusion criteria

Patients meeting all these criteria will be included in the study:

- Age of patient is at least 18 years
- Healthy participants, defined as the absence of active or chronic disease (applicable only to healthy volunteer group).
- Patients are admitted to the ICU or MC after neurosurgery (applicable only to neurosurgery group).

### 4.3 Exclusion criteria

Patient meeting one of these criteria will be excluded from the study:

- patients without a legal representative in case the patient is not able to give informed consent
- pregnant or breast feeding women since there is no adequate data from the use of ALA in pregnant or breast feeding women
- patients with porphyria and/or known photodermatitis
- patients with hypersensitivity to the active substance or to the plaster material of ALA
- insufficient comprehensibility of the Dutch language

#### 4.4 Sample size calculation

The statistical significance level will be set at the 5% level. The sample size will be calculated to achieve a statistical power of 90%. In the pilot study preceding the INOX ICU 2 study, performed on 20 critically ill patients, the mean within-subject variability at the final timepoint (after 24 hours) was 8.7 mmHg with a standard deviation of 5.67 mmHg. In a stable ICU population, a within-subject variability greater than 4 mmHg will be deemed to be less precise. This is pragmatically chosen based on the initial course of within-subject variability calculated in the first 2 hours of measurements. Therefore, the sample size calculation would be as follows:

$$Z_{\frac{\alpha}{2}} = 1.96 \text{ (two tailed for } p = 0.05\text{)}$$

$$Z_{1-\beta} = 1.28 \text{ (for } \beta = 0.10\text{)}$$

$$\mu = 8.7 \text{ mmHg}$$

$$\mu_0 = 4 \text{ mmHg}$$

$$\sigma = 5.67 \text{ mmHg}$$

$$n = \left( \sigma \frac{Z_{\alpha/2} + Z_{1-\beta}}{\mu - \mu_0} \right)^2 = 15.$$

To allow for an expected 10% dropout rate the corrected sample size will be  $15 \times 1.1 = 17$ . The sample size will therefore be 17 subjects for both groups. The study will first commence in healthy volunteers. The study will continue in neurosurgical patients admitted to the ICU and MC of Leiden University Medical Center postoperatively. In 2018, on average 19 postoperative neurosurgical patients were admitted to the ICU / MC of the LUMC per month. For the period March 2019 – June 2019 (matching the period in which this study is expected to be executed) the average was 17.25 admissions per month. Taking these averages into account, 17 neurosurgical patients has been deemed feasible in the allotted time. Further information on the number of admissions of neurosurgical ICU/MC patients can be found in appendix 4.

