### 9.3 Statistical methods to be employed

Descriptive statistics will be used to describe the characteristics of the study population. The mitoPO2 at the different time points will be described with means, standard deviations (SD), medians and interquartile ranges (IQR) (Q1/Q3) as appropriate. For each time point, for each patient, a mean of 5 measurements of mitoPO2 is calculated with a corresponding SD. The mean of these standard deviations will be used to calculate the within-subject variability and the standard deviation of the overall mean per time-point will be used to calculate the between-subject variability.

Normality of variable distribution will be inspected using histograms. Assuming normal distribution of variables, the p values of a paired samples t-test will be reported for comparing overlapping measurement moments between patch 1 and patch 2. If variables are not normally distributed a Wilcoxon signed ranked test will be performed.

Signal quality of the mitoPO2 measurement will be described using the mean and SD of the signal quality. The statistical analysis will be conducted using the SPSS (Statistical Package for the Social Sciences) statistical package, release 23.0 (SPSS Inc., Chicago, IL) and STATA.

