## 14. Appendix 1: Results of the pilot study of the INOX ICU-2 study

**Table 1** The between-subject and within-subject variability of mitoPO2 per measurement moment. The within-subject variability is stable until 2 hours after transfusion, after which an increase is observed

| Measurement moment | Between-subject variability        |                                  | Within-subject variability                                      |
|--------------------|------------------------------------|----------------------------------|-----------------------------------------------------------------|
|                    | Mean mitoPO 2
(mmHg) | SD mitoPO 2
(mmHg) | Mean SD of mitoPO 2 per
measurement moment (mmHg) |
| Before RBC         | 70.5                               | 13.0                             | 3.0                                                             |
| At the end of RBC  | 68.1                               | 11.7                             | 3.4                                                             |
| 15 min after RBC   | 69.5                               | 17.7                             | 3.5                                                             |
| 30 min after RBC   | 68.4                               | 18.7                             | 5.8                                                             |
| 60 min after RBC   | 68.1                               | 15.8                             | 4.6                                                             |
| 120 min after RBC  | 70.0                               | 20.4                             | 3.6                                                             |
| 180 min after RBC  | 67.5                               | 28.2                             | 7.3                                                             |
| 24 hours after RBC | 90.0                               | 42.5                             | 8.7                                                             |

**Fig. 1** Course of mitoPO2 (mmHg) per subject during the measurements. Up to the first hour of measurements the between-subject variability seems stable, afterwards this variability of mitoPO2 increases

[figure not shown]

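### The 90% power in section 4.4 belongs to a one-sample comparison with 4 mmHg that section 9.3 does not contain

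*Protocol*

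**What the plan says.** Section 4.4 of the protocol sets the design values. On the error rate it says "The statistical significance level will be set at the 5% level", and the quantile 1.96 is marked "two tailed for" p = 0.05. On power it says "The sample size will be calculated to achieve a statistical power of 90" percent. The expected value comes from the pilot: "the mean within-subject variability at the final timepoint (after 24 hours) was 8.7 mmHg with a standard deviation of 5.67 mmHg". The reference value is introduced by "In a stable ICU population, a within-subject variability greater than 4 mmHg will be deemed to be less precise", and is described as a pragmatic choice based on the first two hours of pilot measurements. The formula result is given as 15, raised to 17 for 10% dropout, and 17 is used for both groups.

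Section 2.2 calls the study descriptive. Section 9.1 defines within-subject variability, separately per patch, as the mean across participants of each participant's SD at a time point. Section 9.3 repeats this: "The mean of these standard deviations will be used to calculate the within-subject variability". The one inferential procedure in 9.3 is a paired t-test, or a Wilcoxon signed-rank test, between patch 1 and patch 2 at overlapping moments.

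**The concern.** A power statement means something only for a named analysis. Section 4.4 gives a null value, an alternative, an SD, a two-sided level and a power, which together define a one-sample test. The section listing the statistical methods has no such test and no interval for the same quantity. A reader of the eventual report would take 90% as a property of the analysis performed, and it would not be one.

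Section 4.4 also leaves open how the 4 mmHg criterion is to be judged: by point estimate, interval or test. It names no patch, although section 7.2.1 gives both patches a measurement 24 hours after T0. The criterion is worded for a stable ICU population, yet the resulting size is applied to the healthy volunteers as well. If this stays open, the way results are set against 4 mmHg could be chosen after the data are seen.

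**Working it through.** **Inputs (section 4.4).** Alternative mean 8.7 mmHg; reference 4 mmHg; difference 8.7 − 4 = 4.7 mmHg; SD of the per-subject SDs 5.67 mmHg; quantiles 1.96 and 1.28; dropout 10%.

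**Step 1: the plan's own figure.** n = (5.67 × (1.96 + 1.28) / 4.7)² = 15.28. The plan reports 15, so it rounds down; rounding up gives 16. A one-sided version gives 12.5 and does not match, so the calculation is two-sided as stated. For dropout, 15 × 1.1 = 16.5 and 15 / 0.9 = 16.7; both give 17.

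**Step 2: power by the plan's normal formula.** Power = Φ(4.7 × √n / 5.67 − 1.96). At n = 15 this is Φ(3.21 − 1.96) = 89.4%. At n = 16 it is 91.2%, and at n = 17 it is 92.7%.

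**Step 3: power by a one-sample t-test.** The SD would be estimated from the same few subjects, so the noncentral t distribution applies, with noncentrality 4.7 × √n / 5.67. Assuming normally distributed per-subject SDs:

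| Evaluable n | Normal formula | t-test |
|---|---|---|
| 15 | 89.4% | 84.7% |
| 16 | 91.2% | 87.2% |
| 17 | 92.7% | 89.4% |
| 18 | 94.0% | 91.2% |

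**Step 4: sensitivity to shape.** A per-subject SD cannot be negative, and a mean of 8.7 with an SD of 5.67 suggests skew. The documents do not give the distribution, so two shapes with the same mean and SD were assumed. Simulated t-test power at n = 15 is about 94% for a gamma shape and 97% for a lognormal shape. The plausible range at n = 15 is therefore roughly 85% to 97%, depending on shape.

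**Step 5: precision.** The half-width of a 95% interval is t × 5.67 / √n. At n = 15 it is 2.145 × 5.67 / √15 = 3.1 mmHg; at n = 17 it is 2.120 × 5.67 / √17 = 2.9 mmHg.

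**Step 6: the two sections side by side.**

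| | Section 4.4 | Section 9.3 |
|---|---|---|
| Quantity | Mean within-subject SD at 24 hours | Mean within-subject SD at each time point |
| Compared with | 4 mmHg | Nothing |
| Inference on it | Two-sided 5%, 90% power | None; no test and no interval |
| Test named | One-sample (implied by the formula) | Paired, patch 1 against patch 2 |

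**The case against.** The strongest reply is that the study is descriptive. The 4 mmHg figure appears only as a sample-size reference, section 9 has no step that labels a group as less precise, and the analysis plan mentioned in section 11.6 may contain an interval or test. Much of this stands. It rules out any claim that a planned decision rule is faulty. It does not remove the mismatch, because the protocol claims power for one comparison and its own methods section names a different one.

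The arithmetic also has a fair defence. The plan's formula gives 89.4% at 15, which is 90% to within rounding. A reader might infer from the 84.7% that the study is underpowered. The documents do not support that as a firm figure, since it assumes normal per-subject SDs and a t-test that the plan does not specify.

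Three further inferences are tempting and should not be made:

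- **That judging against 4 mmHg is a coin flip.** Any threshold gives about 50% when the truth lies on it, at any sample size. At the design value of 8.7, 99.9% of estimates from 15 subjects would exceed 4 (normal approximation, SD 5.67).
- **That a true value of 6 mmHg could not be told apart from 4.** Power of 25% (n = 15) to 28% (n = 17) follows only if the SD stays at 5.67. If the SD were 0.4 to 0.65 of the mean (an assumption, giving 2.4 to 3.9 mmHg), t-test power at n = 15 would be 85% down to 46%.
- **That 4 mmHg is simply the average of the pilot's early rows.** Appendix 1 says "The within-subject variability is stable until 2 hours after transfusion", and the six rows to 120 minutes average (3.0 + 3.4 + 3.5 + 5.8 + 4.6 + 3.6) / 6 = 3.98. But section 4.4 states no averaging rule, and omitting the 120-minute row gives 20.3 / 5 = 4.06. The origin is a guess.

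**Conclusion.** Wrong as written: an internal inconsistency that should be fixed, not a material arithmetic error. The 90% in section 4.4 is attached to a comparison that section 9.3 does not contain. Were that comparison made with 15 evaluable subjects, power would be 89.4% by the plan's formula and 84.7% by a t-test under normality (89.4% with all 17), and possibly higher with skewed SDs. All these figures take the pilot's 8.7 and 5.67 mmHg as true for both new groups. The enrolment target of 17 per group is not called into question, and no subject is affected.

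**What to change.** Keep 17 per group and change two sections.

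1. **Section 9.3.** Report the mean within-subject SD at 24 hours after T0 with a 95% confidence interval set against 4 mmHg, per group and on one named patch. Base any statement that variability is less precise on that interval and not on the point estimate.
2. **Section 4.4.** Choose one of two routes. Either restate the power with its method and assumptions: 89.4% with 15 evaluable subjects by the normal formula; about 85% by a one-sample t-test with normal per-subject SDs, or 89% if all 17 complete. Or drop the 90% claim and justify the size by precision: a 95% half-width of about 3.1 mmHg with 15 subjects and 2.9 mmHg with 17, at SD 5.67. The second route sits more naturally with a study that section 2.2 calls descriptive, and needs no added hypothesis test.

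The cost is protocol wording, with no extra subjects or measurements. If power is kept and stated for a t-test under normality, the figure is somewhat less favourable than the present one.
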